### Study design

The study is a parallel group prospective double-blind Phase 3 randomised controlled trial comparing a 12-week treatment period of oral CBD (400 mg daily) (Experimental) to placebo (Control), with both groups receiving 4 sessions of manualised CBT-based counselling. Research interviews will be conducted at baseline (week 1), 3-weekly during the study intervention (weeks 4, 7, 10 and 13) and 12-weeks after the end of treatment (week 25) (Fig. 1). The study will use a modified intention-to-treat analysis. The expected number of participants is 250, of which we estimate approximately 20% (*n* = 50) will be of Indigenous background. The study will also include qualitative interviews with Indigenous Australian participants in both control and intervention groups (a total of *n* = 15–25 Indigenous Australian participants) to examine their experiences in the study.

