#### Participant numbers

Sample size calculations are based on the analysis of the primary outcome, that is, the difference between placebo and CBD groups in total number of Cannabis-free Days over the 12-week intervention period. Ferguson has suggested that the minimum effect size (Cohen’s *d*) for an effect of practical clinical significance is 0.4167 [55]. To achieve 90% power (two-tailed) and α = 0.05, a total of *N* = 250 (*n* = 125 per group) participants are needed to detect a between-group effect size of *d* = 0.41. Of the target 250 sample, it is estimated approximately 20% (*n* = 50) of the study sample (*N* = 250) will be Indigenous Australians.

Participants who discontinue study procedures after commencing study interventions (medication dispensed on Day 1) will not be replaced in the study but will be included in the modified intention-to-treat analyses. Participants enrolled and randomised, but do not commence any treatment (no medication dispensed or other clinical interventions) will not be included in the final analysis.

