#### Informed consent, randomisation and blinding

Written informed consent is obtained on Week 1, Day 1 of the study prior to the commencement of all subsequent study procedures. Consent is obtained with the site coordinator independent of treating clinicians, to minimise ‘pressure’ to participate in the study.

The randomisation schedule has been developed by an independent statistician, with eligible participants randomised in a 1:1 ratio between groups using variable block randomisation to help maintain blinding, with subjects stratified by (a) site (to achieve approximately equal numbers of active and placebo at each site) and (b) Indigenous Australian status (to allow direct between-group statistical comparisons within Indigenous Australian participants).

Participants, clinicians, and researchers involved in service delivery, data collection and analysis will remain blinded to study conditions using matched placebos manufactured by the same manufacturer. CBD and placebo will be packaged in identically labelled containers with the participant’s ID number and site. Aside from site trial pharmacists (who have no direct contact with participants), all other members of the clinical or research teams will be blinded to group allocation.

Unblinding will occur after all data are collected, entered, cleaned and the trial database has been locked. In circumstances where allocation needs to be unblinded (e.g. severe adverse event), the principal investigator will authorise the local site investigator to break the blind (via the site trial pharmacist).

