### Data analysis

All data analysis will be performed using Bayesian models instead of frequentist. Bayesian methods can quantify evidence for both effects and the absence of effects, are less prone to non-convergence (due to regularisation), and sample from a joint posterior distribution, hence no family- or experiment-wise correction of regression coefficients for multiple comparisons is necessary [61]. We will use a modified intention-to-treat approach for data analysis, with group membership fixed as the medication type (placebo vs CBD) participants receive on their first study day. Missing data will be imputed via hierarchical multiple imputation [62].

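### The analysis is labelled modified intention-to-treat, but group is defined by the medication received on the first study day and not by the randomised arm (a minor fault with a one-sentence fix)

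*Protocol article*

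**What the plan says.** The analysis population is described in three places in the protocol article.

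- **Study design** gives only the label: "The study will use a modified intention-to-treat analysis".
- **Participant numbers** says what the modification is. People who stop after Day 1 dispensing "will not be replaced in the study but will be included in the modified intention-to-treat analyses". The exclusion reads: "Participants enrolled and randomised, but do not commence any treatment (no medication dispensed or other clinical interventions) will not be included in the final analysis".
- **Data analysis** repeats the label and defines the groups, with "group membership fixed as the medication type (placebo vs CBD) participants receive on their first study day".

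Two features of the design in Informed consent, randomisation and blinding also matter. Allocation has "eligible participants randomised in a 1:1 ratio between groups using variable block randomisation to help maintain blinding", stratified by site and Indigenous status. For dispensing, "CBD and placebo will be packaged in identically labelled containers with the participant’s ID number and site", and only the site trial pharmacists know the allocation.

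The model descriptions use a group variable without defining it again. Primary outcomes names experimental group as the main covariate, and Secondary outcomes carries group into all its models. The sentence in Data analysis is therefore the only definition that applies to them.

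**The concern.** An intention-to-treat comparison, modified or not, keeps each participant in the arm that randomisation assigned. A modification normally concerns who is left out, and Participant numbers states one of that kind. The definition in Data analysis does something else: it lets the product handed over on Day 1 decide the arm.

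For anyone given the wrong product that day, the analysed arm is not the randomised arm. Randomisation no longer protects the comparison for that person, and the label misdescribes what is done. The article states this rule outright, so it is not a detail left to an analysis plan that is not shown. What is at stake is the basis of the efficacy estimate for a few people at most, and a label that readers will take to mean analysis as randomised.

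**Working it through.** **1. Do the sections settle the rule?** Data analysis says medication received. Study design gives the label alone. Participant numbers addresses inclusion and exclusion, not group. The randomisation section describes allocation but not how groups are formed for analysis. Primary outcomes and Secondary outcomes use group undefined. Nothing overrides the as-received definition.

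**2. When do the two rules differ?** Only when the product received on Day 1 differs from the product assigned. Later events cannot matter, because membership is fixed on that day.

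**3. The plan's own figure.** Participant numbers gives "To achieve 90% power (two-tailed) and α = 0.05", and "a total of *N* = 250 (*n* = 125 per group) participants are needed to detect a between-group effect size of *d* = 0.41".

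- Normal approximation: n per group = 2(1.960 + 1.282)² / 0.41², which rounds up to 126 (252 in total), against 125 (250) stated.
- Power at 125 per group: Φ(0.41 × √(125/2) − 1.960) = Φ(3.241 − 1.960) = Φ(1.281) = 0.900.

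The stated size reproduces to within one person per group. It serves below only as a yardstick.

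**4. Possible bias from the as-received rule.** The article gives no error rate, so these inputs are assumptions. Let m participants be moved in one direction, each differing in prognosis from their arm mean by k SD. The arm that gains them has 125 + m people and the arm that loses them has 125 − m. The spurious shift in the contrast is

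m·k/(125 + m) + m·k/(125 − m).

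| m | k | Shift (SD) | Share of d = 0.41 |
|---|---|---|---|
| 1 | 0.5 | 0.008 | 2% |
| 1 | 1 | 1/126 + 1/124 = 0.016 | 4% |
| 2 | 0.5 | 0.016 | 4% |
| 2 | 1 | 2/127 + 2/123 = 0.032 | 8% |
| 5 | 0.5 | 0.040 | 10% |
| 5 | 1 | 5/130 + 5/120 = 0.080 | 20% |

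With k = 0 (errors unrelated to prognosis) the expected shift is zero. The last two rows need five errors, all in the same direction, and are shown only as the far end of the range.

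**5. Cost of grouping by randomised arm.** If a share e of each arm receives the other product, the expected effect by randomised arm is d(1 − 2e). Error rates are again assumed.

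| e in each arm | People of 250 | d | Power at 125 per group |
|---|---|---|---|
| 0 | 0 | 0.410 | 90.0% |
| 0.4% | 1 | 0.407 | 89.5% |
| 1% | 2.5 | 0.402 | 88.8% |
| 2% | 5 | 0.394 | 87.5% |

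Steps 4 and 5 measure different things. The first is the possible bias of the rule as written, and the second is the price of replacing it.

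**The case against.** The best defence is that the important word is the one that fixes membership. The authors may have meant only that group is settled at Day 1 whatever happens afterwards. Table 2 places randomisation and first dispensing in the same Week 1 column, and containers carry the participant's ID, so in practice received on Day 1 and allocated will nearly always coincide. This is a fair account of the likely intent, and it explains why the effect is small. It does not change what the sentence says, and no other section supplies the missing statement. It is also fair that, if errors are unrelated to prognosis, the as-received rule adds no expected bias and avoids the dilution in step 5. But that absence of a link has to be assumed, whereas grouping by randomised arm does not need it.

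A reader might infer more than the article supports:

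- **That the randomised comparison as a whole is broken.** Only a participant misdispensed on Day 1 is affected, and the article reports no such event.
- **That participants could switch arms according to how treatment goes.** Fixing group on Day 1 rules this out, so the usual as-treated problem does not arise.
- **That errors will cluster by site or period and so be tied to outcome.** There are seven sites, and the primary model has no site term, so such clustering would go unadjusted. But nothing in the article says that errors cluster, or that site or period predicts outcome. Errors would also have to run mainly in one direction to move the contrast. The pharmacists who could make an error have no direct contact with participants, which makes a link to prognosis less likely.
- **That the fall in d from 0.41 to about 0.40 is the harm done by the rule.** It is the cost of the fix.

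**Conclusion.** The point holds as a minor fault of definition. The article states an as-received rule under an intention-to-treat label and nowhere says that efficacy follows the randomised arm. Its effect is nil without a Day 1 dispensing error, and nil in expectation unless the people affected differ in prognosis. For one or two people who differ by 1 SD, all moved the same way, the shift is about 0.016 to 0.032 SD, or 4% to 8% of the planned effect. These sizes rest on assumed counts and an assumed prognostic difference. The sample size is unaffected, and excluding participants who start no treatment is not in question here.

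**What to change.** Replace the definition in Data analysis with a sentence saying that, for all efficacy analyses, group is the arm assigned at randomisation, and that the only modification to intention-to-treat is the exclusion, already given in Participant numbers, of participants who start no treatment. Add that medication actually received is used for the safety summaries and, if any Day 1 dispensing error occurs, for a sensitivity analysis of the primary outcomes.

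Make the change before unblinding, so that the rule is not chosen with errors and allocations in view. It costs one or two sentences and no participants. If errors occur there is the slight dilution shown in step 5; if none occur, the results are the same under either rule.

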#### Primary outcomes

We will model the effects of CBD on number of cannabis free days (out of 84 days) via single-level Gaussian regression with the outcome regressed on the main covariate experimental group (placebo vs CBD). Number of cannabis-free days in the 28 days prior to baseline will be included as a covariate to control for variation in participants’ prior frequency of use entering the study. Two treatment factors that could plausibly influence the primary outcomes and which vary across participants will also be included as covariates: number of counselling sessions attended during the study period (count variable range 0–4), and whether or not NRT was taken (binary variable measured at baseline: did not undertake NRT vs undertook NRT). If residuals are distributed normally, we will report the results from this analysis. If residuals are not distributed normally, we will treat cannabis-free days/84 as a bounded count instead of a numeric variable and use aggregated binomial regression with a logit link.

We will model urinary THC-COOH levels (a continuous outcome, in ng/MoL) via random-slopes mixed-effects models with the group, time (6-level categorical ordered predictor; Weeks 1 (baseline), 4, 7, 10, 13), the group × time interaction, number of counselling sessions attended, and whether or not NRT was undertaken as the fixed factors, and participant ID as the random factor.

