### Setting and study sites

The multicenter trial will be coordinated from the Specialty of Addiction Medicine, Faculty of Medicine and Health, University of Sydney (study sponsor). Treatment will be provided at seven specialist addiction outpatient treatment centers: four in Sydney, one in Newcastle and two in Melbourne, Australia.

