#### Statistical methods for Indigenous Australian focussed outcomes

Indigenous Australian and non-Indigenous participants will be compared on baseline participant characteristics (e.g., age, gender, frequency of substance use, scores on quality-of-life scales) via simple regression: Gaussian for continuous measures, Logistic for binary and count variables, and multinomial logistic for multilevel categorical data. For the main study analyses, comparing the frequency of illicit cannabis use between placebo and CBD groups, all participants will be pooled and included in main analyses, irrespective of Indigenous status. However, an additional regression will be performed where Indigenous status and the interaction between Indigenous status and the study drug (Placebo vs CBD), along with the primary predictor study drug, will be included in the regression.

The study will stratify randomisation according to Indigenous status, to achieve an approximately equal number of Indigenous Australian participants on active and placebo conditions, thus requiring no additional statistical procedures beyond those outlined in the previous paragraph.

The effect of the experience of discrimination on outcomes related to cannabis use disorder will be estimated via regressing various outcomes related to cannabis use on scores on the modified Everyday Discrimination Scale (m-EDS). Two regressions will be performed for each outcome, with a different version of the m-EDS as the primary predictor in each: (i) a continuous version of the scale (i.e., total score) and (ii) a three-level categorical version of the scale (no vs low vs moderate-to-high). The outcomes that the m-EDS will be regressed on will be: (i) (baseline characteristics (e.g., years of regular cannabis use, scores on quality-of-life scales), (ii), treatment engagement (e.g., treatment retention, number of counselling sessions) and (iii) outcomes during the trial (e.g., frequency of cannabis use, health measures). As described above, the type of regression will depend on the type of outcome: Gaussian for continuous, logistic for binary or bounded count, ordinal logistic for ordered categorical, and negative binomial for unbounded count. The effect of m-EDS on treatment retention will be estimated via Kaplan Meier plots discrete-time hazard model with complementary log–log link function.

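### The primary cannabis-free-days model omits both stratification factors, site and Indigenous status; if these predict outcome, the interval is somewhat too wide and some precision is forgone

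*Protocol article*

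**What the plan says.** Under Informed consent, randomisation and blinding, the protocol article has participants "randomised in a 1:1 ratio between groups using variable block randomisation", with "subjects stratified by (a) site (to achieve approximately equal numbers of active and placebo at each site) and (b) Indigenous Australian status". Setting and study sites adds: "Treatment will be provided at seven specialist addiction outpatient treatment centers". On Indigenous participants, Participant numbers says that "it is estimated approximately 20% (*n* = 50) of the study sample".

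Under Data analysis, Primary outcomes, the cannabis-free-days model is a "single-level Gaussian regression with the outcome regressed on the main covariate experimental group". Three covariates are added: cannabis-free days in the 28 days before baseline, counselling sessions attended, and whether nicotine replacement was taken. If residuals are not normal, the plan switches to aggregated binomial regression with a logit link. The THC-COOH model has group, time, their interaction, sessions and nicotine replacement as fixed terms, and participant as the random factor. Neither model contains site or Indigenous status.

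Under Statistical methods for Indigenous Australian focussed outcomes, the main analyses pool everyone irrespective of Indigenous status. A further regression adds Indigenous status and its interaction with study drug. The next paragraph says that stratification by Indigenous status should give roughly equal numbers in the two arms, "thus requiring no additional statistical procedures beyond those outlined in the previous paragraph".

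**The concern.** Stratified allocation balances the strata between arms, so differences between strata largely drop out of the treatment contrast. A model without the strata still counts those differences as residual error. The estimated effect then varies less from trial to trial than its reported standard error says. Balance through stratification is therefore a reason to put the factor in the model. The sentence on Indigenous status reasons the other way.

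This is a stated choice and not a detail left for a later document. The covariates are listed, and a single-level model rules out a random effect for site. The supplementary regression does not fill the gap. It is not the primary analysis, and because it contains the interaction, its study-drug coefficient under ordinary reference coding is the effect in one stratum, not the adjusted overall effect.

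At stake is precision on the outcome that drives the sample size. The gain from adjusting rests on two variables that are already recorded for randomisation.

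**Working it through.** **Inputs from the protocol article.** 1:1 allocation in variable blocks; seven sites; about 20% Indigenous; 125 per group; d = 0.41; two-sided alpha 0.05; power 90%. Participant numbers states the design as "To achieve 90% power (two-tailed) and α = 0.05" and says that 250 "participants are needed to detect a between-group effect size of *d* = 0.41".

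**Input not in the documents.** R², the share of outcome variance that the strata explain. It is assumed here from 0 to 0.20, with total SD fixed at 1. For the planned model, read it as the share left unexplained by the covariates already included.

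**Step 1: the plan's own figure.** n per group = 2(1.960 + 1.282)²/0.41² ≈ 125.0, which rounds up to 126. Power at 125 per group is 0.9000 by the normal formula and 0.898 by the noncentral t. The stated 250 reproduces.

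**Step 2: effect of omitting the strata (Gaussian model, normal approximation).**
- Standard error reported without the strata: SE = √(2/125) = 0.1265
- True standard error under stratified allocation: SE_true = SE × √(1 − R²)
- Interval width ratio: 1/√(1 − R²)
- Type I error without the strata: 2[1 − Φ(1.960/√(1 − R²))]
- Power without the strata: Φ((0.41 − 1.960 × SE)/SE_true)
- Power with the strata: Φ(0.41/SE_true − 1.960)

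Example, R² = 0.10: SE_true = 0.1265 × 0.9487 = 0.1200. Power without is Φ((0.41 − 0.2479)/0.1200) = Φ(1.351) = 91.16%. Power with is Φ(3.417 − 1.960) = Φ(1.457) = 92.74%.

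| Assumed R² | Width ratio | Type I error, without | Coverage, without | Power, without | Power, with | Difference (points) |
|---|---|---|---|---|---|---|
| 0 | 1.000 | 5.00% | 95.00% | 90.0% | 90.0% | 0 |
| 0.02 | 1.010 | 4.77% | 95.23% | 90.22% | 90.56% | 0.34 |
| 0.05 | 1.026 | 4.43% | 95.57% | 90.57% | 91.40% | 0.83 |
| 0.10 | 1.054 | 3.88% | 96.12% | 91.16% | 92.74% | 1.58 |
| 0.15 | 1.085 | 3.35% | 96.65% | 91.77% | 94.01% | 2.24 |
| 0.20 | 1.118 | 2.84% | 97.16% | 92.40% | 95.19% | 2.79 |

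**Step 3: simulation check.** Ordinary least squares, N = 250, seven sites of equal expected size, 20% Indigenous. Block sizes of 2, 4 and 6 are assumed, as is a split of R² into three quarters site and one quarter Indigenous status. There were 6000 null and 3000 alternative trials per setting. At R² = 0, 0.05, 0.10 and 0.20:
- Type I error without the strata: 5.1%, 4.1%, 4.4%, 3.0%
- Type I error with the strata: 5.0%, 4.6%, 5.5%, 5.2%
- Power without: 90.1%, 90.9%, 90.5%, 92.2%
- Power with: 90.2%, 92.0%, 92.4%, 95.6%

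The pattern agrees with Step 2 apart from simulation noise. The standard error of a simulated 5% rate is √(0.05 × 0.95/6000) = 0.28 points. At R² = 0 the mean standard error is 0.1264 without the strata and 0.1265 with them, so adjusting costs almost nothing even when the strata are uninformative.

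**The case against.** The strongest reply is that the harm depends on an unknown. The documents give no intraclass correlation or stratum effect. Baseline cannabis-free days may already absorb much of what the strata carry, and counselling is manualised and delivered by trained psychologists. The higher prevalence and harms reported for Indigenous Australians do not by themselves predict a different trial outcome. With weak strata the loss is close to nil. This stands, which is why the table starts at zero. It bears on the size of the loss and gives no reason for the omission.

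Several stronger readings are tempting but not supported:

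- **That the primary test is invalid.** In the Gaussian model the error is conservative. Type I error falls below 5%, and power without the strata stays at or above the planned 90%.
- **That the gain from stratifying is thrown away.** Stratification still reduces the true variance of the contrast. Only the part that an adjusted standard error would recognise goes unused.
- **That the plan declares adjustment for site unnecessary.** The sentence concerns Indigenous status only, and it excepts a regression that contains that factor. On site, the plan is silent.
- **That THC-COOH is equally affected.** Baseline is a level of time and participant is random, so the group-by-time contrast already removes stable differences in level between sites or by Indigenous status. Only differences in change over time remain.
- **That every secondary model needs six site indicators.** In logistic models with few events, these could be unstable and would make the odds ratio conditional on site.

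**Conclusion.** The point holds, mainly for cannabis-free days, and its size is modest. The randomisation uses two factors that the primary model leaves out, and the reason given for Indigenous status is not a sound one. If the strata explain 5% to 10% of the remaining variance, the interval is about 3% to 5% wider than needed and power is about 0.8 to 1.6 points lower than with adjustment. At 20% the figures are about 12% and 2.8 points; at zero nothing is lost.

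This rests on the assumed R², a normal approximation with total SD held fixed, and near-complete balance within strata. All analyses are planned as Bayesian, so the error rates and power are frequentist analogues that carry over only approximately, under weak priors. The figures do not cover the binomial fallback, where the variance formula does not apply and where, with a logit link, adding or omitting a prognostic factor also changes the odds ratio being estimated.

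**What to change.** - **Cannabis-free days:** add Indigenous status as a fixed term and site as a random intercept or six indicators. With a random intercept, the model is no longer single-level and the text should say so. Carry the same terms into the binomial fallback and state that the odds ratio is then conditional on them. If the factors are to stay out, give a reason.
- **THC-COOH:** add the same terms for consistency, expecting a smaller gain.
- **Sparse binary secondary outcomes:** use a random intercept for site, or shrinkage, and not six free indicators.
- **Indigenous-focused methods:** reword the sentence so that balance through stratification is no longer the reason that the main analysis needs no adjustment. Keep the interaction regression as a supplementary analysis.

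The cost is a change of wording before unblinding. No new data are needed. Adjustment uses at most seven degrees of freedom out of 250 (six for site, one for Indigenous status), or one random effect and one coefficient. With only seven sites, the prior on the between-site SD should be stated.
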